
### Additional measures

Baseline demographic and medical information will be reported: age, gender, ethnicity, marital status, education level, tinnitus duration, hearing loss, sleep, other audiological problems, other health problems and previous treatments. Previous research has indicated that sleep can change with age, so age will be included in the final model as a covariate.Use of psychotropic and hypnotic medications will be collected at each time point. If participants commence such medication, their results will be excluded from analysis. We will report numbers of any such changes across all groups.Use of night-time sound enrichment, naps, caffeine and alcohol will be collected at each time point because the offer of sound generators and advice regarding sleep hygiene is a systematic difference between treatment groups. We will report proportions of participants using night-time sound enrichment across groups, and we will also report proportions of patients showing reductions in caffeine, alcohol and naps across groups.One participant per treatment arm per cohort will be randomly allocated an Actiwatch to wear during the same time period as sleep diary completion. This will provide an objective comparator for the subjective diary data. This measure is limited because there is insufficient hardware available to include all participants.

Following treatment, participants will indicate the usefulness and relevance of treatment on 11-point Likert scales (0 to 10). They will be asked to provide qualitative feedback regarding their experiences and views of treatment.

A diagrammatic representation of the trial process (enrolment, intervention and assessment) is shown in the Standard Protocol Items: Recommendations for Interventions (SPIRIT) diagram (Fig. 2). For the full SPIRIT checklist, please see supplementary material Additional file 1.

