### Inclusion and exclusion criteria

Participants are eligible if they report:
Presence of insomnia for a minimum of 3 months (scoring 15 or more on the ISI);At least moderately distressing tinnitus for at least 6 months (scoring 8 or more on the Mini-Tinnitus Questionnaire [Mini-TQ]);Sleep problems directly related to tinnitus;Absence of organic sleep disorders (as assessed by a sleep disorder screening questionnaire);Tinnitus has been fully assessed by a doctor/audiology specialist;Aged between 18 and 70 years;English proficiency and hearing level allow for participation in a group; andWilling and able to provide informed consent to take part in a sleep-focused group treatment.

Participants will be excluded if they report:
Current, comorbid, severe physical or mental illness;Active risk of harm to self or others;Current substance dependence;Current/planned pregnancy or breastfeeding; andMedical investigations into sleep or tinnitus incomplete.

Participants taking hypnotic or psychotropic medication at the point of consent will be asked to keep this stable for the duration of the trial and not to engage in additional psychotherapy.

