### Randomisation and blinding

Treatment will be group-based, with group sizes including six participants, on average. Treatment will be delivered in cohorts, with three groups, one for each arm of the study, running in parallel. Randomisation will be done using a customised computer algorithm for each cohort separately. The study requires individual randomisation with stratification for gender. Within each cohort, stratification will be used to ensure groups are comparable in gender composition. Because group size will be small per cohort, it was decided that stratification for age was not appropriate to run per cohort. Instead, age differences will be checked post-randomisation per group to ensure there are no significant group differences in age in each cohort.

Randomisation of consented participants will take place 3 weeks prior to the commencement of intervention. Age, gender and participant number will be provided to an independent party, who will use a computer-based random number sequence generation to allocate group. Allocation information will be returned to the research assistant, who will then notify participants of their group allocation (group 1, 2 or 3). Participants will only be informed of the treatment associated with their group number when they arrive at the first session. It is not possible to blind participants or therapists to allocation; however, participants will be blind to the content of the other therapies. Statistical analysis will be conducted by an independent statistician who will be blind to group (i.e., provided with group number, not group type).

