### Primary outcome analysis

The ISI and sleep diary data will be analysed using linear mixed models, accounting for repeated measures on participants and the cluster structure of the trial. Post hoc comparisons of independent groups will allow multiple comparisons by using adjusted *P* values. We will also conduct an analysis to indicate the number needed to treat based on reliable change in the ISI.

Analysis will be based on modified intention to treat (excluding those who contribute no data). For data missing at random, multiple imputation will be used. To minimise missing data, the research assistant will follow up on missing data after questionnaire completion.

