### Sensitivity and other planned analyses

Additional sensitivity analysis will be conducted as follows: outliers (analyses with and without outliers), non-compliance (a per-protocol analysis), baseline imbalance (analyses with and without adjustment for baseline characteristics, if imbalanced), and impact of distributional assumptions (analysis plan will assume a normal distribution for continuous outcomes, and this will be tested for goodness of fit in the analysis). In addition, sensitivity analyses will be conducted using other suitable distribution under further statistical advice.

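### Results of participants who start hypnotic or psychotropic medication after randomisation are excluded, which conflicts with the stated modified intention-to-treat analysis and creates a risk of bias of unknown sign

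*Protocol article*

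**What the plan says.** Two sections of the protocol article decide whose data enter the analysis.

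- **Additional measures.** "Use of psychotropic and hypnotic medications will be collected at each time point". The next sentence sets the rule: "If participants commence such medication, their results will be excluded from analysis". The only reporting attached to it is a count: "We will report numbers of any such changes across all groups".
- **Primary outcome analysis.** "Analysis will be based on modified intention to treat (excluding those who contribute no data)". Gaps are to be filled: "For data missing at random, multiple imputation will be used".

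Three other sections bear on how these fit together.

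- **Inclusion and exclusion criteria** asks people already on such drugs to hold them steady: "Participants taking hypnotic or psychotropic medication at the point of consent will be asked to keep this stable for the duration of the trial". It does not mention the analysis set.
- **Randomisation and blinding** fixes the order of events: "Randomisation of consented participants will take place 3 weeks prior to the commencement of intervention". Participants learn which treatment they have only at the first session.
- **Sensitivity and other planned analyses** lists "non-compliance (a per-protocol analysis)" among the sensitivity analyses, without mention of medication starters.

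**The concern.** Methods/design places all four assessments after randomisation, at 3, 10, 14 and 34 weeks. A rule triggered by medication use recorded at those visits is therefore a post-randomisation exclusion. Entry requires an ISI of 15 or more, so a participant whose sleep does not improve has an obvious reason to seek a hypnotic. Participants and therapists are unblinded, so starting may also depend on the arm. If so, the rule selects on something related to the primary outcome, possibly to a different degree in each arm, and randomisation no longer protects the comparison of those who remain.

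Three results are exposed: the CBTi-ABC difference on ISI, sleep efficiency and total sleep time; the proportions with reliable change (Hypothesis 2A); and the number needed to treat. For the last two, removing a starter who is a non-responder lowers the denominator and leaves the numerator unchanged, so that arm's response rate rises.

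Two incompatible statements of the analysis set also leave the choice between them open until results are known.

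**Working it through.** **1. The two rules side by side.** Take a participant who returns ISI and diary data at weeks 3 and 10 and is recorded as having started a hypnotic at week 14.

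| Rule | Treatment of this participant |
|---|---|
| Primary outcome analysis | Kept: has contributed data |
| Additional measures, all data dropped | Removed, including valid week-10 data |
| Additional measures, only data after the start dropped | Person kept, observed later outcomes removed |

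The wording does not say which of the last two is meant. On either, observed outcomes that the modified intention-to-treat definition would keep are dropped.

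**2. The plan's sample size.** Inputs from Sample size: d = 0.8, significance level 5% (two-sided assumed), power 80%, groups of 6, within-group correlation 0.07, correlation between measures 0.25, loss to follow-up 10%.

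- Unadjusted n per arm: 2 × ((1.96 + 0.842)/0.8)² = 24.53
- Design effect: 1 + (6 − 1) × 0.07 = 1.35
- Baseline-adjustment factor: 1 − 0.25² = 0.9375
- n per arm: 24.53 × 0.9375 × 1.35 / 0.9 = 34.5, rounded up to 35

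The stated 34 is reproduced to within one participant. The 10% is described as loss to follow-up, so exclusions for medication come on top of it.

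**3. Effect on power.** Analysed per arm before medication exclusions: 34 × 0.9 = 30.6. Standard error: √(0.9375 × 1.35 × (1/n₁ + 1/n₂)). Power: Φ(0.8/SE − 1.96). Start rates are assumptions; the document gives none.

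| Starters excluded, CBTi / ABC | Power |
|---|---|
| none | 79% |
| 5% / 5% | 77% |
| 5% / 15% | 75% |
| 10% / 10% | 75% |
| 5% / 20% | 74% |

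These figures ignore any bias.

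**4. Possible bias.** Assume a normal outcome and a threshold model in which the tendency to start medication has correlation r with poor outcome, the same in both arms. Excluding a fraction p of starters raises an arm's mean by r × φ(c)/(1 − p), where c is the upper-p normal quantile.

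- p = 0.15: φ(c)/(1 − p) = 0.274
- p = 0.05: φ(c)/(1 − p) = 0.109
- Difference before multiplying by r: 0.166 SD

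With a true difference of 0.8 SD, in original SD units:

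| Start rates, CBTi / ABC | r = 0.3 | r = 0.5 | r = 0.7 |
|---|---|---|---|
| 5% / 5% or 10% / 10% | 0.80 | 0.80 | 0.80 |
| 5% / 10% | 0.77 | 0.76 | 0.74 |
| 5% / 15% | 0.75 | 0.72 | 0.68 |
| 5% / 20% | 0.73 | 0.68 | 0.63 |
| 10% / 20% | 0.75 | 0.72 | 0.69 |

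At 5% / 15% the raw difference shrinks by 0.05, 0.08 and 0.12 SD. At r = 1, where the starters are exactly the worst outcomes, it shrinks by 0.17 SD, the ceiling for these rates in this model. Swapping the rates (15% CBTi, 5% ABC) gives the same amounts with the sign reversed, so the effect is overstated.

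**The case against.** The strongest reply is that the documents show no bias. They give neither start rates nor reasons for starting. The rule covers psychotropic as well as hypnotic drugs, and a psychotropic may be started for reasons unrelated to sleep. A start in the three weeks before treatment cannot reflect treatment failure. Someone who starts a hypnotic may even score as an ISI responder. All of this stands. A reader might infer that the rule deletes treatment failures and biases the CBTi-ABC result in a known direction; the text supports only a risk.

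A reader might also take 0.17 SD, about one fifth of the assumed 0.8, as the likely size. That requires starting to be determined entirely by outcome. Trimming the tails also reduces the SD of those analysed, to about 0.80 in ABC and 0.90 in CBTi (pooled 0.85). The standardised difference in that scenario is then 0.634/0.851 = 0.74, about 7% below 0.8. In that scenario the error also runs against CBTi.

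Next, if only results after the start are dropped, the person stays in the modified intention-to-treat set, and the mixed model and imputation could handle the gap. That is a fair reading and weakens any claim that two different sets of people are defined. It does not remove the conflict: observed outcomes are still discarded, and the article does not say that this is how the rule works.

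Finally, the effect in the absence of new medication is a legitimate question. But excluding the starters answers it poorly, and it is not the question that the declared modified intention-to-treat analysis asks.

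**Conclusion.** The point holds as an unreconciled contradiction about which data are analysed, with a consequent risk of bias of unknown size and sign. The contradiction needs no assumption: one section excludes on a post-randomisation event, the other excludes only for absence of data, and the planned per-protocol sensitivity analysis is not linked to the medication rule.

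The size rests wholly on assumed start rates, a normal outcome and an equal correlation in both arms. Under 5% (CBTi) and 15% (ABC), the raw difference shrinks by 0.05 to 0.12 SD for correlations of 0.3 to 0.7, with 0.17 SD as the ceiling. It is about zero when starting is equally frequent and equally outcome-related in both arms, and it favours CBTi if CBTi has more starters. The loss of power, from about 79% to between 77% and 74% under the assumed rates, is modest and secondary.

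**What to change.** Reconcile Additional measures with Primary outcome analysis before the data are analysed:

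1. Remove the medication exclusion from the primary analysis. State that every randomised participant with data is analysed in the allocated arm, whatever medication is started. Apply the same set to the reliable-change proportions and the number needed to treat.
2. Move medication-based handling to a labelled sensitivity analysis. Setting ISI and diary values after the start to missing, and imputing them under a stated assumption, is preferable to excluding participants. Whichever is used, say whether it affects all of a person's data or only data after the start.
3. Report medication starts by arm, as already planned.

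The cost is a change of wording and one sensitivity analysis. Medication use is already collected at each time point, so completed recruitment is no obstacle. The change concerns the analysis set only and leaves medication management as it is.

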**Fig. 2 Fig2:**
[figure not shown]
SPIRIT diagram

### Sample size

We calculated the sample size required to test the primary hypothesis on the basis of a recent meta-analysis of 14 randomised controlled trials comparing CBTi with control groups in the treatment of primary insomnia [22]. Here, between-group comparisons reported effect sizes on subjective sleep variables (Cohen’s *d*) as ranging from medium (*d* = 0.44) to large (*d* = 1.09) across a range of control groups (including no intervention, placebo control, waiting list, treatment as usual and information controls). Similarly, medium to large effect sizes were seen on self-rating measures. When looking at treating insomnia in the context of a chronic health condition such as pain, similar moderate to large effect sizes are reported [27]. These findings have led us to base a power analysis on an assumed effect size of 0.8.

Estimation of potential loss to follow-up was set at 10%, based on rates reported by Okajima et al. [22], as ranging from 0% to 33% and as 8% from a clinical evaluation of CBTi within a tinnitus clinic [31]. We assumed a cluster design with six patients per group, and we assumed a within-group correlation of 7%, estimated from a previous study [31]. Correlation between measures was estimated as 25% on the basis of a small pilot study. It is likely that the true correlation will be higher, so this estimate has a conservative effect on required sample size. Assuming a significance level of 5% and 80% power, the number of participants needed to detect a statistically significant difference between the CBTi and ABC groups on the primary measures of interest was 34 per group (102 across all three groups).

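### The 34 per arm makes no allowance for having only about six therapy groups per arm; at the stated inputs the CBTi–ABC contrast has about 75% power, not 80%

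*Protocol article*

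**What the plan says.** The Sample size section of the protocol article sets out to "base a power analysis on an assumed effect size of 0.8". It then gives the other inputs:

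- Loss: "Estimation of potential loss to follow-up was set at 10" per cent.
- Clustering: "We assumed a cluster design with six patients per group, and we assumed a within-group correlation of 7" per cent.
- Correlation: "Correlation between measures was estimated as 25% on the basis of a small pilot study". The authors add that the true value is probably higher, which would make the estimate conservative.
- Error rates: "Assuming a significance level of 5% and 80% power".

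The result is 34 per arm and 102 in total, for the CBTi versus ABC comparison. No formula is named, and no correction for the number of clusters is mentioned.

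Two other sections matter. Randomisation and blinding puts the average therapy-group size at six and says: "Treatment will be delivered in cohorts, with three groups, one for each arm of the study, running in parallel". Primary outcome analysis specifies "linear mixed models, accounting for repeated measures on participants and the cluster structure of the trial".

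**The concern.** Everyone in a therapy group receives the same treatment, so the CBTi–ABC difference is estimated between groups. The precision of that estimate has to be judged from the variation among therapy groups, and 34 per arm in groups of about six gives only about 6 groups per arm, or 18 in all.

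A design effect enlarges the variance to reflect clustering. It does not reflect the fact that this variance is itself estimated from few clusters. The planned model will meet that second problem, because it includes the cluster structure. The sample size appears to deal only with the first. If so, the stated 5% level and 80% power do not both hold at the stated inputs, and a null result would be read against more power than those inputs give.

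**Working it through.** **Inputs.** From Sample size: d = 0.8, alpha 5% (two-sided assumed, since the article does not say), power 80%, m = 6 per group, ICC 0.07, r = 0.25, loss 10%. From Randomisation and blinding: one group per arm per cohort, averaging six people.

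**Reproducing the 34.**

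- Two-mean normal formula: 2(1.96 + 0.8416)²/0.8² = 24.53 per arm.
- Design effect: 1 + (6 − 1) × 0.07 = 1.35.
- Baseline-adjusted, with loss: factor 1 − 0.25² = 0.9375, so 24.53 × 0.9375 × 1.35/0.9 = 34.5. With groups of 5.4 after loss, the design effect is 1.308 and the result is 33.4.
- No baseline adjustment and no loss: 24.53 × 1.35 = 33.1.
- Individual-level t formula × 1.35: 34.5 without baseline adjustment or loss; 36.0 with both.
- Change score: factor 2(1 − 0.25) = 1.5, so 24.53 × 1.5 × 1.35 = 49.7 before loss. This does not reproduce.

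Every variant that lands within two of 34 uses either a known variance or individual-level degrees of freedom.

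**Power with the clusters counted.** Take the favourable baseline-adjusted contrast at one post-treatment time point.

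- Analysed per arm: 34 × 0.9 = 30.6.
- Groups per arm: 34/6 = 5.7, taken as 6.
- Between-group degrees of freedom: 3 × (6 − 1) = 15 when all three arms are fitted together; 2 × (6 − 1) = 10 when only two are.
- Standard error in SD units: √(2 × 0.9375 × DE/30.6), with DE = 1 + (m − 1) × 0.07.
- Noncentrality: 0.8 divided by that standard error.
- Power: noncentral t, with two-sided 5% critical values 2.131 (15 df) and 2.228 (10 df).

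| Group size m | DE | SE | Noncentrality | Power, z | Power, 15 df | Power, 10 df |
|---|---|---|---|---|---|---|
| 5.1 (30.6/6) | 1.287 | 0.281 | 2.85 | 81% | 76% | 73% |
| 5.4 (6 × 0.9) | 1.308 | 0.283 | 2.83 | 81% | 75% | 72% |
| 6 (as stated) | 1.350 | 0.288 | 2.78 | 79% | 74% | 71% |

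Solving the same expression for 80% power on 15 df gives a detectable effect of 0.84 to 0.86.

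**Simulation.** In 4,000 simulated trials per setting (10% random loss), the three-arm mixed model with Satterthwaite degrees of freedom had 74–75% power. At its empirically exact 5% critical value it had 77.5%. With z critical values it had 79% power at 5.7% type I error. A separate simulation of 200,000 balanced trials (m = 5.1) gave 75.6% for the Satterthwaite-type test, and 80.0% power at 5.8% type I error for z.

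**Sensitivity to the correlation.** Replace 0.9375 by 1 − r², keeping 30.6 analysed and 15 df. At r = 0.40 (factor 0.84) power is 78–80%. At r = 0.45 (factor 0.7975) it is 80–82%. These two values of r are assumptions; the article gives only 0.25.

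**The case against.** Five points can fairly be made against this.

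- **The 34 is not miscalculated.** This is right. It follows from the stated inputs, and clustering and loss are both in it. What is missing is a small-sample allowance. The formula is inferred, since none is named, but power at 34 per arm in about 6 groups can be worked out directly without knowing it.
- **A reader might infer power as low as 70%, ten points short.** That needs a two-arm fit on about 10 df. The article does not plan one: Primary outcome analysis describes mixed models followed by comparisons between groups, and Secondary outcome analysis refers to three-group differences as in the primary analysis. This points to one three-arm model, for which the gap is roughly 3–6 points.
- **The correlation of 0.25 is described as conservative.** This stands as real mitigation. A true value of about 0.40–0.45 would restore 80% on 15 df. The article gives the direction but no figure, and its 80% is claimed at 0.25.
- **A reader might infer that the trial will run at a 6% type I error.** That holds only for a z reference. Nothing in the article specifies one, and the choice is commonly left to the analysis plan, which is not shown.
- **The calculation uses one post-treatment contrast.** The primary outcome also spans the two follow-ups, and a contrast pooled over time would have different power. This limits how exactly the shortfall can be stated.

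**Conclusion.** The point holds, at modest size. At the article's own inputs, a valid 5% test of CBTi against ABC from a three-arm mixed model has about 74–77% power. A two-arm fit would have about 71–73%. The most favourable variant, which ignores the article's own 10% loss and keeps baseline adjustment, gives 78–79% on 15 df. No valid choice of degrees of freedom restores 80% at the stated inputs.

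This rests on d = 0.8, ICC 0.07, r = 0.25, 30.6 analysed per arm in about 6 groups, a two-sided test and a single baseline-adjusted post-treatment contrast. The planned adjusted P values and the use of three primary measures are not counted. The documents do not support calling the trial badly underpowered, nor calling the 34 an arithmetic error.

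**What to change.** Keep 102 participants; the article reports recruitment as already complete.

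In Sample size, restate power for the CBTi–ABC contrast as about 75% at d = 0.8 and r = 0.25 with about 6 therapy groups per arm, or give the detectable effect at 80% power as about 0.84–0.86. Add that about 80% is reached if the correlation is about 0.40–0.45.

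In the primary analysis, estimate the contrast from one mixed model containing all three arms and a random therapy-group effect, with Kenward–Roger or Satterthwaite degrees of freedom, unless the analysis plan already says so. By the formula, the three-arm fit gains about 3 points over a two-arm fit (74–76% against 71–73%).

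The cost is one or two sentences and one model setting. The downside is a slightly less favourable stated power.
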